## Abstract

**Background:**

Low back pain remains a costly quality-of-life-related health problem. Microdiscectomy is often the surgical procedure of choice for a symptomatic, single-level, lumbar disc herniation in younger and middle-aged adults. The question of whether a post-microdiscectomy exercise program enhances function, quality of life, and disability status has not been systematically explored. Thus, the overall purpose of this study is to assess immediate and long-term outcomes of an exercise program, developed at University of Southern California (USC), targeting the trunk and lower extremities (USC Spine Exercise Program) for persons who have undergone a single-level microdiscectomy for the first time.

**Methods/design:**

One hundred individuals between the ages of 18 and 60 who consent to undergo lumbar microdiscectomy will be recruited to participate in this study. Subjects will be randomly assigned to one of two groups: 1) one session of back care education, or 2) a back care education session followed by the 12-week USC Spine Exercise Program. The outcome examiners (evaluators), as well as the data managers, will be blinded to group allocation.

Education will consist of a one-hour "one-on-one" session with the intervention therapist, guided by an educational booklet specifically designed for post-microdiscectomy care. This session will occur four to six weeks after surgery. The USC Spine Exercise Program consists of two parts: back extensor strength and endurance, and mat and upright therapeutic exercises. This exercise program is goal-oriented, performance-based, and periodized. It will begin two to three days after the education session, and will occur three times a week for 12 weeks.

Primary outcome measures include the Oswestry Disability Questionnaire, Roland-Morris Disability Questionnaire, SF-36^® ^quality of life assessment, Subjective Quality of Life Scale, 50-foot Walk, Repeated Sit-to-Stand, and a modified Sorensen test. The outcome measures in the study will be assessed before and after the 12-week post-surgical intervention program. Long-term follow up assessments will occur every six months beginning one year after surgery and ending five years after surgery.

Immediate and long-term effects will be assessed using repeated measures multivariate analysis of variance (MANOVA). If significant interactions are found, one-way ANOVAs will be performed followed by post-hoc testing to determine statistically significant pairwise comparisons.

**Discussion:**

We have presented the rationale and design for a randomized controlled trial evaluating the effectiveness of a treatment regimen for people who have undergone a single-level lumbar microdiscectomy.

## Background

Approximately 12–33% of the adult work force is affected by low back pain each year, and it has been suggested that between 70% and 95% of adults will suffer from low back pain at some time during their lifetime [1-5]. Unlike other orthopedic disorders, the expenses associated with management of back pain have increased over the last 20 to 30 years [1,2]. A recent study on health care expenditures for people with back pain in the United States reported that total expenditures were over $90 billion in 1998, and that these individuals incurred 60% higher expenditures than those without back pain [6]. Despite continuous clinical and scientific efforts, low back pain remains an ever-present, quality-of-life-related, health problem.

The lumbar intervertebral disc is susceptible to injury and early degeneration, which often result in pain and disability. To effectively remedy these problems, treatment of symptomatic lumbar disc herniations has continuously evolved. Surgeons have sought to reduce operative trauma to the spine by adopting minimally invasive techniques such as microdiscectomy, (microscope-assisted or endoscopic), which is used to treat single-level disc injury in working-age adults. Despite widespread use of this technique, there are few reports of long-term results [7-10]. Early success rates ranging from 70–91% have been reported [7,11-14]. Limited available data related to long-term follow-up demonstrates that the success rate decreases to 60–70% after three to ten years [8]. However, these success rates may be influenced by post-operative care.

The current practice pattern for management of activity post-operatively has three distinct directions. A common, but not studied, approach includes 4 to 16 weeks of limited activity following the surgery. A second approach, advocated more recently by Carragee et al [15], suggests that eliminating post-operative activity restriction leads to enhanced short-term outcomes for patients after limited open discectomy. A third approach incorporates an early strengthening intervention into the post-surgical regimen [16-19].

A limited number of studies have evaluated the impact of trunk strengthening programs on functional outcomes following lumbar disc surgery. These studies varied in sample size (21–96 subjects), intervention period (4–12 weeks), and follow-up period (0–52 weeks after surgery) [16,18-21]. While the data suggest that longer interventions (three months) have a greater impact on disability status of subjects than shorter interventions [16,18,19,22], the relatively short follow-up periods make it difficult to assess the long-term effects of an exercise intervention on function, quality of life, disability status, or pain. The paucity of detail in published studies regarding the specifics of the interventions creates a challenge to researchers and clinicians attempting to reproduce the protocols.

In summary, the question of whether a post-microdiscectomy exercise program enhances long-term function, quality of life, and disability status has not been systematically explored. Thus, the overall purpose of this study is to assess immediate (after12 weeks of intervention) and long-term (up to 5 years) outcomes of a strengthening and endurance physical therapy program targeting the trunk and lower extremities for persons who have undergone a single-level microdiscectomy for the first time.

We hypothesize that compared to patient education only, a focused intervention combining muscle strengthening and endurance exercise with patient education will result in immediate and long-term improvement in selected physical measures, function, and quality of life, and will reduce pain and disability in people status-post single-level lumbar microdiscectomy.

## Methods/design

The Institutional Review Board of the University of Southern California (USC) granted approval for this randomized controlled trial. The organizational infrastructure includes a central data management and analysis team, a scientific advisory panel, and a data monitoring and safety board (Figure 1). The study coordinator and recruiter will communicate with surgical practices, physical therapy clinics, and prospective subjects. Blinded-to-group-allocation evaluators will administer all face-to-face measurements (primary and secondary outcome measures) after completing standardization training in the testing procedures. These "blinded," standardized testers will be videotaped during mock trials and their performance will be scored by other research associate examiners on their ability to administer the protocol as instructed. Standardized testers will have scored at least 90% on a checklist of competencies during mock trials before they will be permitted to test the study subjects. Physical therapists in participating clinics ("intervention therapists") will complete standardized training in the intervention procedures, including instruction of the education session and the exercise program. These intervention therapists must pass a videotaped mock intervention session with a score of 90% on a checklist of competencies before they will be permitted to administer interventions to the subjects.

The study is divided into three phases, a protocol development phase, an implementation or intervention phase, and a follow-up phase. During the protocol development phase, a team of physical therapist researchers and clinicians developed, tested, and standardized the post-surgical intervention and testing protocols. During the intervention phase, a two-group, pretest-posttest design will be used, with participants being randomly assigned to one of two groups: one session of back care education, or a back care education session followed by the 12-week USC Spine Exercise Program. This design will allow for the analysis of the effects of treatment over time. The outcome measures in the study (see below) will be assessed before and after the post-surgical intervention period. The evaluators, as well as the data managers, will be blinded to group allocation. After the end of the intervention phase, follow-up assessments of selected outcome measures will be conducted on all participants every six months, beginning one year and ending five years after the date of surgery (the follow-up phase). The follow-up phase will allow for the analysis of the stability of the effect of treatment over time.

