### Data analysis

The primary and secondary outcome measures will be assessed for immediate and long-term effects using two-factor multivariate analysis of variance (MANOVA), with repeated measures for time. For all multivariate ANOVA tests described, significant main effects will be reported if there are no significant interactions. If significant interactions are found, then one-way ANOVAs will be performed for each main effect. Post-hoc testing will be performed (as necessary) to determine statistically significant pairwise comparisons. Statistical analysis of the results will be performed using the SAS system, version 8.2 (SAS Institute Inc., Cary, NC, USA). All significance levels will be set at p < 0.05.

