### Sample size

Power calculations were based on data from prior published studies [23,24,42,44,57]. These data indicated that the inter-subject variability with respect to impairments, activity, and participation, was moderate to high. Since the outcome measures assess the immediate and long-term effects of rehabilitation in addition to surgery, the calculations were made on the assumption that the changes due to exercise and education will be greater than those expected for education alone. A 50% difference between groups (education, and exercise plus education) is expected based on prior studies, and a 30% subject attrition rate is anticipated. The possible attrition rate is attributed to length of the rehabilitative program, elimination of symptoms, or increase of symptoms and need for a second surgery. All power calculations were based on an alpha level of 0.05 and power of 0.8. Therefore, accounting for attrition, each group would need approximately 50 subjects.

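### The follow-up phase is meant to analyse whether the treatment effect is stable, but the long-term testing rule neither estimates nor reliably tests change in the between-arm difference after the intervention

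*Protocol article*

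**What the plan says.** Methods/design states what the long follow-up is for: "The follow-up phase will allow for the analysis of the stability of the effect of treatment over time". The Background makes outcomes up to five years part of the overall purpose and hypothesises immediate and long-term improvement over education alone.

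Under Data analysis, the primary and secondary outcomes are to be "assessed for immediate and long-term effects using two-factor multivariate analysis of variance (MANOVA), with repeated measures for time". The levels of time are not given. The rule then branches. On one side, "significant main effects will be reported if there are no significant interactions". On the other, "If significant interactions are found, then one-way ANOVAs will be performed for each main effect". After that, "Post-hoc testing will be performed (as necessary) to determine statistically significant pairwise comparisons", and "All significance levels will be set at p < 0.05".

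All measures are taken before the intervention, after it and at 1 year (Outcome measures). Later contacts are by post, and a participant who reports no symptoms is sent only the physical activity scale (Follow-up period).

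**The concern.** Stability is a statement about one quantity: the between-arm difference late in follow-up minus the between-arm difference just after the intervention. The rule under Data analysis never forms that quantity as an estimate. Whether it tests it depends on an unstated choice of time points, and the consequence of a non-significant result is to report one effect over all visits.

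If the rule is followed literally, a lasting benefit and a vanished one can both arrive as a significant interaction, or a benefit that has halved can be reported as a single average effect. Whether the benefit lasts is the reason for following patients beyond the 12-week programme, so the long-term conclusion could be wrong in either direction. The immediate comparison is not affected.

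**Working it through.** **Inputs from the article.** About 50 per group and 30% attrition (Sample size), so 50 × 0.7 = 35 evaluable per arm; alpha 0.05 (taken as two-sided); three visits with all measures.

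**The plan's own figure.** The article says "All power calculations were based on an alpha level of 0.05 and power of 0.8" and "A 50% difference between groups (education, and exercise plus education) is expected based on prior studies", but gives no SD or control value, so 50 per group cannot be reproduced. It follows if the SD is about 0.74 of the reference mean: 0.5/0.74 ≈ 0.68 SD, which 35 per arm detect with 80% power, and 35/0.7 = 50.

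**Assumptions.** One continuous outcome, SD 1 at each visit, equal between-visit correlation ρ = 0.3 / 0.5 / 0.7, complete data, effects of 0.5 or 0.68 SD. Results below are in that order of ρ.

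**1. Pre-intervention visit included.** Between-arm differences at the three visits are (0, d, d) if the effect is kept and (0, d, 0) if it is lost. Under equal correlations the noncentrality of the interaction test is λ = (n/2) × Σ(δ − mean δ)² / (1 − ρ).
- Kept: the mean is 2d/3, and the squared deviations sum to 4d²/9 + d²/9 + d²/9 = 2d²/3.
- Lost: the mean is d/3, and the sum is d²/9 + 4d²/9 + d²/9 = 2d²/3.

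The two are identical. With d = 0.5 and n = 35, λ = 17.5 × 0.1667 / (1 − ρ) = 4.17 / 5.83 / 9.72. The multivariate test (F with 2 and 67 df) then has power 0.41 / 0.55 / 0.78 in both cases. The omnibus p-value cannot tell a kept effect from a lost one.

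**2. Follow-on tests by visit.** One-way ANOVAs and pairwise comparisons, as described, compare arms at a visit or visits within an arm. At d = 0.5 a single visit is significant with probability 0.54. If visits were independent, significance after 12 weeks and non-significance at 1 year would occur in 0.54 × 0.46 ≈ 25% of trials with a constant effect. With ρ = 0.3 / 0.5 / 0.7, simulation gives about 20% / 17% / 12 to 13%.

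**3. Post-intervention visits only.** With two visits the interaction is a t test of the change in effect. The SD of a within-person change is √(2(1 − ρ)) = 1.18 / 1.00 / 0.77, and the standard error of the between-arm difference in change is that × √(2/35) = 0.283 / 0.239 / 0.185.
- Halving from 0.68 to 0.34 SD: noncentrality 0.34/SE = 1.20 / 1.42 / 1.84 on 68 df, power 0.22 / 0.29 / 0.44. The loss is missed in 78% / 71% / 56% of trials.
- Complete loss of a 0.5 SD effect: missed in 59% / 46% / 24%.
- 95% CI half-width: 1.995 × SE = 0.56 / 0.48 / 0.37 SD. Under equal correlations the pre-intervention value is uncorrelated with the later change (covariance ρ − ρ = 0), so adjusting for it leaves these widths essentially unchanged.

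**The case against.** The strongest reply is that stability is not a stated hypothesis. Methods/design says only that follow-up permits its analysis. The Background hypothesises improvement, and for that a group-by-time test including the pre-intervention visit is conventional. Levels of time, contrasts and any margin could sit in a fuller plan that is not shown. This stands in part: the absence of a margin or a named contrast is not in itself a fault. What remains is that the article fixes a branching rule for long-term effects, and that rule does not serve the use it gives for the follow-up phase.

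Several stronger inferences are tempting and are not supported:
- That the interaction is the only planned test. Main effects, one-way ANOVAs and pairwise comparisons are planned too. At 35 per arm a 1-year comparison rejects in about 54% of trials if a 0.5 SD effect is kept, against 5% if it is lost. That is informative, though it is not a test of change.
- That a stable effect always makes the interaction significant. It makes it non-zero; in the three-visit scenarios at 0.5 and 0.68 SD, rejection ranges from about 41% to 97%. Nor is this a type I error, since a real effect is present.
- That no reading tests stability. With post-intervention visits only, the interaction is the right contrast.
- That the authors will call p > 0.05 stable, or read significance followed by non-significance as loss. The text says neither; the risk is that nothing in it prevents either reading.

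**Conclusion.** The concern holds in a limited form. On one reading of the time factor, the omnibus test cannot separate a kept effect from a lost one, and the follow-on tests do not compare differences between visits. On the other reading, the right contrast is tested with power of about 0.22 to 0.44 against loss of half of a 0.68 SD effect, and a non-significant result is followed by a pooled main effect. Only one reading can apply, and neither yields an estimate of the change with its uncertainty.

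The figures rest on one outcome, 35 complete cases per arm, assumed effects of 0.5 and 0.68 SD, and equal correlations of 0.3 to 0.7. The exact equality of power is particular to three visits with equal correlations. That a lasting effect is itself an interaction, once the pre-intervention visit is included, does not depend on these values. The calculations stop at 1 year; later visits are limited first by sending symptom-free participants only the activity scale. The change should be made, but the plan's immediate comparison does not depend on it.

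**What to change.** In Data analysis, name the long-term stability analysis: the baseline-adjusted exercise-minus-education difference at 1 year minus the same difference at the post-intervention visit. Estimate it from one model of the post-intervention visits with the pre-intervention value as covariate, and report it with a 95% CI. Add that neither a non-significant interaction nor a move from significant to non-significant between visits will be read as stability or loss. Contrasts after 1 year should be claimed only where the outcome is collected regardless of symptoms.

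A numerical margin for calling the effect stable is optional and for the sponsor to choose. As an illustration, ruling out loss of half of a 0.67 SD effect (0.335 SD; one-sided 0.025, 80% power, no true change) needs 4(1 − ρ) × 7.85 / 0.335² ≈ 196 / 140 / 84 evaluable per arm at ρ = 0.3 / 0.5 / 0.7.

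The cost is a few sentences and one contrast per outcome, with no new patients or data. The downside is that, with a half-width of about 0.37 to 0.56 SD, stability will often have to be reported as inconclusive.

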### Study sample

One hundred individuals between the ages of 18 and 60 who consent to undergo lumbar microdiscectomy will be recruited to participate in this study. Potential subjects will be medically screened, pre- and post-surgically, by one of 27 surgeons who have been informed about the study. Patients deemed eligible for the study based on the medical screening, will be offered the opportunity by the surgeon's nurse coordinator to consult with a study coordinator regarding participation in the study. The nurse coordinator will complete an eligibility screening form on each individual screened for the study, and the study coordinator will track the number of potential participants screened and the reasons for exclusion from the study.

If the potential participant agrees to meet the responsibilities of the study, an enrollment appointment will be scheduled with a "blinded" evaluator. The evaluator will review the informed consent, and a summary of the Health Insurance Portability and Accountability Act of 1996 (HIPAA) policy, in detail with prospective participants. The purpose of the study, the procedures to be employed, any potential risks and benefits of participation, random placement into one of two groups, and the responsibilities of the participants and the members of the research team, will be discussed with the potential participants. All questions regarding the study will be answered fully. When the individual signs the consent form, the evaluator will initiate testing of the outcome measures. Successful completion of the evaluation will be reported to the study coordinator, who will inform the study participant about his or her group allocation. The study participant will choose one of the 17 participating clinics as the site of care delivery.

There will be no enrollment restrictions based on gender, race, or ethnic origin. There is no reason to expect that this study population will not reflect an adequate racial cross-section of Los Angeles and surrounding communities.

### Inclusion and exclusion criteria

The participating surgeons will screen patients for pre-surgical inclusion and exclusion criteria. The primary pre-surgical inclusion criteria include: diagnosis of disc protrusion confirmed by magnetic resonance imaging (MRI) testing, predominant symptoms in the lower extremity, radicular pain distribution, restricted straight-leg raise, and positive signs of adverse nerve-root tension (i.e., impaired mobility and/or pain and/or dysesthesia). Pre-surgical exclusion criteria include symptoms suggestive of facet arthrosis or neurogenic claudication, and plane radiographs showing more than 50 percent loss of disc height at the relevant spinal level. Patients in whom the protrusion occupies more than 50 percent of the sagittal diameter of the spinal canal or in whom sequestrated fragments are seen on MRI will also be excluded.

Individuals over the age of 60 will be excluded to control for the confounding effects of spinal osteoarthritis. Pediatric subjects will not be recruited for this study, as performing microdiscectomies in children is contraindicated.

Other pre-surgical exclusion criteria include: previous back surgeries, presence of any concurrent lower extremity pathology (other than that associated with low back and lower extremity pain associated with single level disc injury), neurological disorders (e.g., stroke, dementia, seizures), cognitive dysfunction (e.g., traumatic brain injury, cerebrovascular accident, Alzheimer's disease), uncontrolled cardiovascular disease, evidence of spinal cord compression, uncontrolled hypertension, infection, severe respiratory disease, pregnancy, rheumatic joint disease, peripheral vascular disease with sensory loss at the foot, or any condition the subject identifies that might limit participation in physical activity.

To continue in this study, the primary post-surgical inclusion criterion is that the subject must have undergone a single level (L3–4, L4–5, or L5–S1) microdiscectomy that was without adverse event four to six weeks after the surgery. All subjects must be willing to participate upon enrollment.

### Interventions

The interventional protocol comprises two components: education and exercise. The protocol is based on extensive literature review, best evidence available, and clinical expertise of those who developed the protocol, with input from consultants.

Education will consist of a one-hour "one-on-one" session with the intervention therapist, and will occur in a time window four to six weeks after surgery. Exercise will consist of two parts: 1) isometric trunk strength and endurance training, and 2) mat and upright therapeutic exercises. The exercise protocol will begin during the session following the education session (two to three days later), and will occur three times a week for 12 weeks.

